# Ultrasound-guided erector spinae plane block versus thoracic paravertebral block on postoperative analgesia after laparoscopic nephroureterectomy: study protocol of a randomized, double-blinded, non-inferiority design trial

**DOI:** 10.1186/s13063-021-05173-0

**Published:** 2021-04-06

**Keywords:** Erector spinae plane block, Thoracic paravertebral block, Regional anesthesia and analgesia, Pain control, Laparoscopic urological surgery

## Abstract

**Introduction:**

Erector spinae plane block (ESPB) is a novel inter-fascial plane block, which is applied more and more in postoperative pain control, especially in chest surgery. Regional block is advocated in order to decrease opioid consumption and improve analgesia in urological surgery. Therefore, we aimed to explore whether ESPB would have similar analgesia compared with thoracic paravertebral block (TPVB) in laparoscopic nephroureterectomy.

**Methods and analysis:**

This prospective, randomized, double-blinded, non-inferiority trial will enroll 166 patients undergoing laparoscopic nephroureterectomy. Participants will be randomly assigned 1:1 into receiving ESPB or TPVB before surgery. Both ultrasound-guided ESPB and TPVB will be performed with an injection of 0.375% ropivacaine 0.4 ml/kg before anesthesia induction. Standardized patients controlled intravenous analgesia (PCIA) will be applied for each patient. The primary endpoint is the joint of cumulative 24 h opioid (sufentanil) consumption and average pain score via numeric rating scale (NRS) at 24 h after surgery. Secondary endpoints include rescued analgesic demand, cumulative opioid consumption, and pain NRS scores at different preset timepoints within 48 h after surgery. Other predefined outcomes include clinical features of blockage, quality of recovery, subjective sleep quality, time to ambulation and diet, and adverse events, as well as length of stay in hospital and anesthesia cost.

**Discussion:**

Previous studies investigating the analgesic efficacy of ESPB only concentrated on a single endpoint for postoperative pain evaluation, while studies focusing on the direct comparison between ESPB and TPVB in urological surgery are still lacking. Our study is the first trial in non-inferiority design of comparing ESPB and TPVB in patient undergoing laparoscopic nephroureterectomy, and the primary outcome is the joint endpoint of opioid consumption and pain NRS score.

**Trial registration:**

Chinese Clinical Trial Registry ChiCTR 2000031916. Registered on 14 April 2020.

**Supplementary Information:**

The online version contains supplementary material available at 10.1186/s13063-021-05173-0.

## Strengths and limitations of this study

Our study is the first trial in non-inferiority, double-blinded design of comparing ESPB with TPVB for analgesia in laparoscopic nephroureterectomy.The primary outcome in our study is set as a joint endpoint of opioid consumption and pain NRS scores, both of which are deemed equal important in evaluating pain control.This study will investigate not only erector spinae plane block efficacy of analgesia, quality of postoperative recovery as usual, but also its clinical features of blockage.The relatively small sample size may limit to discriminate the safety consideration between the two blocks technique.A single-center trial design may limit its universality.

## Introduction

Upper tract urothelial carcinoma (UTUC) includes carcinoma of the renal pelvis and ureter, as well as bladder. According to the study of European and American population, UTUC accounts for 5–10% of all urothelial carcinoma [1], while this proportion may be higher in China. Laparoscopic nephroureterectomy is increasingly gaining popularity for UTUC therapy due to its advantages of less invasive, faster recovery, and fewer complications. Briefly speaking, this technique is started with detaching the ureter and kidney, and then ligating the renal artery and vein through laparoscopic approach, subsequently resecting the distal ureter, partial bladder, and retrieving all specimens through a 5–8-cm arc or McBurney’s incision in the ipsilateral lower abdomen.

A previous study has shown that patients often suffered moderate to severe pain after laparoscopic nephroureterectomy [2]. Adequate pain control is crucial for postoperative recovery [2]. The traditional analgesia is mainly based on opioids. However, opioids were associated with adverse effects such as respiratory depression, nausea and vomiting, itching, and dizziness, and some patients may be forced to abandon opioids for the reason of intolerance. Thus, multimodal analgesia including trunk block covering the incisions in lateral and anterior abdomen is advocated to enhance early recovery after laparoscopic nephroureterectomy.

Thoracic paravertebral block (TPVB) is a classic trunk block with definite analgesic effect for both somatic and visceral pain. Its efficacy has been demonstrated in urological surgery [3–5].

Erector spinae plane block (ESPB) is a novel inter-fascial plane block first introduced by Forero et al. in 2016 [6], providing wide-ranging analgesia in lung surgery [7–9], laparoscopy [10], mastectomy [11], and pediatric surgery [12, 13]. The proposed mechanism of ESPB is that distribution of local anesthetic solution spreads into the paravertebral space and epidural space [14], which then blocks the dorsal, ventral, and traffic branches of spinal nerve. However, a few studies disagreed [15, 16].

Compared with TPVB, ESPB has the following advantages. First, the dermatomal distribution of sensory loss is extensive, which covers the area ranging from the ipsilateral parasternal to the midline of the lower back in a single shot block. It has been reported that ESPB performed at T5 level can give a sensory loss dermatome from T2 to T9 [6, 17], while local anesthetic solution spreading cranially to the upper thoracic level and caudally as far as the L2-L3 level is founded in ESPB performed at T7 level [18]. Second, regarding to safety, ESPB is conducted in shallow layer and far away from important organs and blood vessels; therefore, the risk of pneumothorax [19, 20], hematoma, nerve injury, and other complications involves less than TPVB theoretically. Finally, when it comes to the simplicity and convenience, the ultrasound imaging features of muscle layers and transverse processes are easy to identify and locate [21].

Although studies have shown that ESPB has a better analgesic effect comparing with traditional opioid intravenous analgesia, there is still a lack of evidence in direct comparing the analgesic efficacy between ESPB and TPVB in urological surgery. Besides, most of previous studies just chose a single endpoint for postoperative pain evaluation and the follow-up period is often limited within 24 h after surgery. Our study is the first trial in non-inferiority design in comparing of ESPB and TPVB with a 48 h follow-up after surgery in patient undergoing laparoscopic nephroureterectomy, and the primary outcome is a joint endpoint of opioid consumption and pain NRS (numeric rating scale) scores.

### Study objectives

The aim of this study is designed to compare ESPB with TPVB in terms of the efficacy of analgesia, the quality of postoperative recovery, and clinical features of blockage in laparoscopic nephroureterectomy. We hypothesize that the analgesic efficacy of ESPB is non-inferior to that of TPVB for patients undergoing laparoscopic nephroureterectomy.

## Methods

### Study design

This trial is a prospective, single-center, two-arm, double-blinded, non-inferiority randomized controlled trial. The study is initiated by Peking University First Hospital, and its design has been completed in strict accordance with the SPIRIT 2013 statement (see Additional file 1 for the SPIRIT Checklist).

The protocol of this trial has been approved by the Clinical Research Ethics Committee of Peking University First Hospital (registration number: 2019-333) on 29 March 2020 with the latest version 1.1. This trial has been registered on Chinese Clinical Trials registry (identifier: ChiCTR2000031916). We will strictly adhere to the Good Clinical Practice guidelines and the Declaration of Helsinki during the whole period of the study. The flowchart diagram of the study is illustrated in Fig. 1, and the SPIRIT figure of enrolment, interventions, and assessments is presented in Table 1.

**Fig. 1 Fig1:**
[figure not shown]
Flowchart of the study

**Table 1 Tab1:**
[figure not shown]
Content and timelines for the schedule of enrolment, interventions, and assessments

**PRE* preoperative, *POS* postoperative

***NRS* numeric rating score

### Participants

On the day before surgery, patients will be screened by an investigator according to the inclusion/exclusion criteria. If the operation is on Monday, the screening will be performed on the previous Friday. Written informed consent will be obtained from each participant before the enrolment. Patients will be instructed how to self-assess pain severity via the numeric rating scale (NRS, an 11 points scale where 0 = no pain and 10 = most severe pain).

#### Inclusion criteria

Participants who meet all of the following criteria will be enrolled in this study:
Between 18 and 75 years of age;Plan to undergo laparoscopic nephroureterectomy;Agree to receive regional nerve block and postoperative intravenous controlled analgesia (PCIA);American Society of Anesthesiologist (ASA) physical status classification I–III.

#### Exclusion criteria

Participants will be excluded if they have any of the following conditions:
Refuse to participate in this study;BMI > 35 kg/m^2^ or < 15 kg/m^2^;Combined with severe comorbidities, including but not limiting to renal dysfunction (creatinine > 442 μmol/L or requirement of renal replacement therapy), liver dysfunction (Child-Pugh class C) and heart failure, or ASA physical status classification ≥ IV;Contraindication of deep nerve block, including but not limiting to be allergic to anesthetic drug, coagulation disorder, and infection at the injection site;Chronic opioids dependence or chronic pain over 3 months;Unable to communicate preoperatively due to severe dementia, language barrier, or neuropsychiatric disorder;Unable to perform nerve block procedure due to difficult anatomy through ultrasound scan.

### Randomization, allocation concealment, and blinding

#### Randomization

The SAS 9.3 software package (SAS Institute, Cary, NC, USA) is used to generate random numbers with a block size of 4 by biostatisticians who will not participant in the statistical analysis of the data. The random sequence will be sealed in consecutively numbered opaque envelopes and kept by the study coordinator. Participants will be randomly divided into two groups according to the 1:1 ratio of ESPB group and TPVB group. A research coordinator is designated to distribute and preserve randomization result. The coordinator will open the envelopes for allocation according to the order of enrolment and prepare the study drug.

#### Blinding

The participants will be blinded to the allocation. Because the needle injection of ESPB and TPVB are very close, participants themselves could hardly detect the clinical differences. Anesthesiologists who perform the nerve block and take charge of intraoperative management and surgeons are independent individuals. Only the random sequence number rather than the specific nerve block type will be recorded in the electronic anesthesia information management system (AIMS). Researchers who do not take part in the nerve block and intraoperative management are designated to postoperative follow-up. Besides, trained anesthesiologist who do not perform the block will be designated to evaluate the clinical features of the block objectively. When case report forms (CRFs) are written and checked, the data will be monitored periodically by the Clinical Research Ethics Committee of Peking University First Hospital. After the database is locked, allocation will be handed over and revealed to statistical analysis.

### Intervention

Participants will be admitted to the preoperative preparation area 30 min earlier before transferring to operating room (OR). After establishment of standard monitoring and intravenous access, premedication with 0.02 mg/kg midazolam or 0.08 μg/kg sufentanil will be administrated if necessary. Before regional block, all patients will be positioned lateral decubitus with the operative side up and received ultrasound scan by two experienced anesthesiologists who will not take part in perioperative management and follow-up. After being confirmed as suitable participants for nerve block, patients will receive ultrasound guided ESPB or TPVB block according to the randomized grouping allocation. The drug used for both interventions is the same with a bolus of 0.375% ropivacaine in the volume of 0.4 ml/kg. Once the block is completed, the dermatomes of sensory loss will be assessed by ice-tactus tests every 5 min. Both the onset time (defined as the time to the first detection of a blocked dermatome) and time to fixed sensory block (defined as the time when there was no further extension of the blocked dermatomes) will be recorded. Decreased or loss off thermic sensation of any region will be regarded as successful sensory loss (the illustration for predefined regional distribution was attached in Additional File 2).

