### Safety consideration

We will strictly adhere to the steps to minimize the risk of adverse events which might be caused by regional nerve block. First, we will scan eligible patients before the enrolment and exclude those who are difficult for TPVB and ESPB from anatomical point of view. Both blocks will be performed under directly ultrasound guiding by experienced anesthesiologists. Second, the local anesthetic we used for regional block is 1.5 mg/kg ropivacaine (0.4 ml/kg with 0.375% in our study), which has already been proved to be safe in previous studies [24, 25]. Third, regional block will be performed only after intravenous access and standard monitoring are established; therefore, we can detect any adverse events timely. Lastly, participants will be continuously monitored till 24 h after surgery. Researchers will follow-up the participants at preset timepoints after surgery, and all adverse events occurred during this period will be carefully managed and severe adverse events will be reported to the Clinical Research Ethics Committee as soon as possible. If the patient’s harm level meets the insurance claims, payment will be arranged as soon as possible.

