### Secondary endpoint

For the opioid consumption and pain NRS scores at other different timepoints after surgery, repeated measure ANOVA (analysis of variance) will be performed if normality and homogeneity of variance and sphericity hypothesis (Mauchly’s test) are met. If not, one-way ANOVA and its correction (Greenhouse-Geisser coefficient correction and Huynh-Feldt coefficient correction) as well as generalized estimated equation (GEE) model will be performed. As for inter-group comparison, independent sample *t* test will be used for comparison if the distribution accords normality assumption; if distribution is skewed as well as not independent at different timepoints, the difference will be determined by Mann-Whitney *U* test.

Outcome analyses will be performed in the intention-to-treat (ITT) population, i.e., all patients are analyzed in the group to which they are randomized and received at least part of study intervention. A per-protocol (PP) analysis will be also performed for the primary endpoint. Statistical analysis will be performed by professional biostatisticians. All conclusions will be based on the original data.

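### The protocol does not fix the ultrasound exclusion before envelope opening, and a fixed block of 4 leaves up to a third of allocations predictable when eligibility is judged

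*Protocol article*

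**What the plan says.** Five parts of the protocol article bear on this point.

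- **Participants and Exclusion criteria.** An investigator screens patients on the day before surgery (the Friday before, for Monday operations), and consent precedes enrolment. The last exclusion criterion is anatomy on ultrasound that makes the block too difficult. No objective threshold is given.
- **Intervention.** In the preparation area, after monitoring, intravenous access and possible premedication, two experienced anesthesiologists scan the patient. They take no part in perioperative management or follow-up. Then: "After being confirmed as suitable participants for nerve block, patients will receive ultrasound guided ESPB or TPVB block according to the randomized grouping allocation".
- **Safety consideration.** Here the order is stated relative to enrolment: "we will scan eligible patients before the enrolment and exclude those who are difficult for TPVB and ESPB".
- **Randomization.** The list uses "random numbers with a block size of 4". On concealment: "The random sequence will be sealed in consecutively numbered opaque envelopes and kept by the study coordinator". On release: "The coordinator will open the envelopes for allocation according to the order of enrolment and prepare the study drug". Nothing links release to the scan.
- **Statistical analysis, Secondary endpoint.** The ITT population is defined as "all patients are analyzed in the group to which they are randomized and received at least part of study intervention".

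**The concern.** An eligibility decision that rests on judgement should be final before anyone can know the arm, and should be hard to influence by guessing it. The text secures neither.

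First, the sections do not settle whether the envelope is still sealed when the scan is read. If enrolment is taken to be complete after the day-before screening and consent, the envelope may be opened before the scan on the day of surgery.

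Second, with a short fixed block at one center, staff who give the blocks learn the arms they deliver and can work out some of the later ones.

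The judgement could plausibly depend on the arm. The Introduction presents easily identified ultrasound landmarks as an advantage of ESPB over TPVB, so borderline anatomy might be declared too difficult more readily when TPVB is known or expected. A non-inferiority conclusion rests on comparable arms, and arm-dependent exclusion would undermine that comparability. A patient excluded after allocation would have received no intervention and would leave the analysis set under the stated ITT definition.

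**Working it through.** The plan states no figure on this point, so there is none to reproduce. The check has two parts.

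**1. Order of steps**

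| Section | What it fixes | What it leaves open |
|---|---|---|
| Participants | Screening on the day before; consent before enrolment | When enrolment is complete |
| Exclusion criteria | Difficult anatomy on scan excludes | When the scan is done |
| Safety consideration | Scan and exclusion before enrolment | Day and place |
| Intervention | Scan on the day of surgery, suitability confirmed, then block | Whether the envelope is already open |
| Randomization | Envelopes opened in enrolment order | Any link to the scan |

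Two sequences fit this text:

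- **A:** screening and consent, scan on the day, enrolment, envelope, block. Exclusion precedes allocation. This follows the Safety consideration section.
- **B:** screening, consent and enrolment on the day before, envelope, scan on the day, block. Exclusion can follow allocation. This fits Participants, Randomization and Intervention, but conflicts with Safety consideration.

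Under B, a patient excluded at the scan is randomised but untreated, and so falls outside the ITT set as defined. The per-protocol analysis would not restore that patient.

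**2. Predictability, which remains under A**

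Inputs: block size 4 and 1:1 allocation (Randomization), one center (Study design), 166 patients (Sample size calculation). Assumption: the guesser knows the block size and every earlier arm.

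A 1:1 block of 4 has 6 equally likely sequences. By position:

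| Position | P(certain) | P(best guess right) |
|---|---|---|
| 1 | 0 | 1/2 |
| 2 | 0 | 2/3 |
| 3 | 1/3 (first two equal) | 1/3 × 1 + 2/3 × 1/2 = 2/3 |
| 4 | 1 | 1 |

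- Certain: (1/3 + 1)/4 = 33.3%.
- Best guess right: (1/2 + 2/3 + 2/3 + 1)/4 = 70.8%, against 50% with no information.
- 166 patients make 41 complete blocks (164 patients) plus 2. Certain allocations: 41 × 4/3 = 54.7, about 55. Correct guesses in the 164: 164 × 0.708 = 116, against 82 by chance.

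For comparison, a fixed block of 6 gives 25.0% certain and 68.3% guessed correctly. Lengthening a known block therefore helps little; varying the size and not disclosing it matters more.

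**From predictability to exclusions.** The scan-exclusion rate is not given. If it were 1% to 5% (an assumption), exclusions judged while the next arm was certain would number about 166 × 0.01/3 = 0.6 to 166 × 0.05/3 = 2.8. Each would also need a judgement swayed by the arm.

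**The case against.** The strongest reply is that the article already contains a safe order. Safety consideration puts the scan before enrolment, and envelopes follow enrolment. The Intervention section runs the same way, from scan to confirmation to block. Participants dates the screening, not the enrolment. Nowhere is an envelope said to be opened before the scan. This stands: a reader might infer that patients are excluded with their arm known, and the documents do not establish that. It is one permitted reading. What remains is that Intervention and Randomization never place the envelope relative to the scan, and only the Safety section's wording stands against sequence B.

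A reader might also take it as stated that the scanning anesthesiologists give the blocks. The text does not say so. It is a strong inference, because Intervention keeps those two out of perioperative management and follow-up, and Blinding separates the people who perform the blocks from others. It remains an inference.

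The exclusion wording is not explicitly tied to the assigned block, which also counts in the plan's favour. But no section plainly requires suitability for both blocks whichever is assigned.

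The 1/3 figure needs full knowledge of earlier arms and of the block size. Sealed, opaque, numbered envelopes held by a coordinator are a real safeguard against reading the next allocation, though not against deducing it. The block size cannot be assumed to stay unknown: the article that states it was published on 6 April 2021, and recruitment ran from 27 April 2020 to an expected end of 30 May 2022.

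Finally, the ITT definition is partly a separate matter: under sequence A it removes nobody excluded at the scan. And a condensed article may leave operational timing to the full protocol. The point here is narrower, namely that the article's own sections pull in different directions and that it fixes a short constant block.

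**Conclusion.** The point holds in limited form. The sections do not agree clearly on when the anatomical exclusion is made relative to enrolment, and envelope opening is not tied to the scan. Exclusion after allocation is therefore permitted on one reading, and the ITT definition would then take that patient out of the primary analysis. On the safer reading, up to 1/3 of allocations are certain and about 71% can be guessed correctly, provided one person knows the block size and all earlier arms.

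The count of about 55 might be read as the number of patients affected by bias. It is not: it is a ceiling on predictable allocations. The number excluded at the scan is unknown. The documents do not show that difficult sonographic anatomy is related to sufentanil use or pain score, so neither the size nor the direction of any bias can be given. The weakness is worth correcting because it is avoidable and touches the comparability of the arms. It is not evidence that the comparison has been compromised.

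**What to change.** 1. Reconcile Participants, Randomization, Intervention and Safety consideration so that all state one order: the scan result, recorded as suitable for both ESPB and TPVB, completes eligibility, and only then does the coordinator open the envelope. This removes knowledge of the arm at the scan. The cost is a wording change and, if envelopes are now opened earlier, a reordered step in the preparation area.
2. For the unused part of the sequence, use randomly varying block sizes (for example 4 and 6) and do not disclose them to the staff who scan or give blocks. This reduces guessing, which step 1 alone does not address. The cost is regenerating the list and the remaining envelopes during recruitment, a small but real task.
3. Define ITT as all randomised patients, analysed by assigned arm. This keeps in the analysis any patient who is allocated but not blocked. The cost is a wording change.

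None of these adds staff or patient procedures.
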